### Stages of primary outcome analysis

We will adopt a transparent and simple cohort approach to the analysis of the primary outcome. Our approach to inference will consider whether it is plausible that DREAMS+PrEP had an impact on HIV incidence among the target population [28, 29].

We will conduct our primary analysis in three phases. Each stage aims to build the strength of the evidence base of a plausible causal impact of DREAMS on HIV incidence. In phase one, we will take an individual-level cohort analysis approach. At 24-months, we will describe the number of women retained in the cohort and summarise follow-up time (average and total) in the DREAMS+PrEP and comparison sites. We will describe HIV incidence at 24 months in the DREAMS+PrEP and comparison groups with associated 95%CI. We will also describe site-specific estimates of incidence. Using Poisson regression, we will compare the incidence rates at 24-months across the two groups expressed as an unadjusted rate ratio with associated 95%CI presented. To account for the RDS design, we will weight the data by 1/self-reported degree of social network.

The unadjusted rate ratio is subject to confounding by risk factors for HIV that are differential across the two groups in the absence of random allocation and the small number of sites. In phase two, we will estimate a rate ratio adjusted for potential confounders. We will present the adjusted rate ratio with associated 95%CI.

In the third phase, we will assess whether there is evidence for an association between individual-level exposure to DREAMS+PrEP interventions and HIV incidence. For example, we will compare the risk of HIV infection between women self-reporting that they are adherent to PrEP and women who did not take PrEP. We will specify the exact measures of exposure after the year 1 data have been collected, without reference to the outcome data and before the final follow-up.

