### Key considerations for study design

We seek to estimate the impact of the DREAMS+PrEP intervention on HIV incidence among YWSS aged 18–24. The DREAMS+PrEP intervention includes identifying high risk women, referral for an offer of PrEP for those testing negative, and referral to other DREAMS interventions, depending on need and availability, that will support use and adherence through a variety of behavioural and structural interventions. This impact evaluation has four main design challenges. First, it was not possible to randomise study sites to receive the DREAMS intervention. DREAMS districts were selected through country-level consultation and based on population of AGYW and HIV burden. Second, YWSS, the target group for this evaluation are a “hidden” population for which a sampling frame does not exist. Third, there are few intervention districts, and 80% of the intended beneficiaries that fall within our target group will be recruited from only two districts. Fourth, there are numerous providers and the strategies to identify, reach and refer YWSS to services is complex.

Our overall approach to these design challenges is to: 1) use existing data (from the *Sisters* programme) to select comparison sites comparable to the DREAMS+PrEP sites in factors known to influence HIV risk; 2) leverage the use of the network-based (respondent driven) strategy that is being used to identify and reach YWSS, refer these YWSS to services, in order to recruit them into the impact evaluation, and repeat this process in the non-DREAMS comparison sites; 3) take a cohort analysis approach to compare HIV incidence among YWSS in the DREAMS+PrEP sites with YWSS in the non-DREAMS comparison sites, and collect data on recent infection and risk factors for HIV incidence at enrolment in support of an adjusted analysis; 4) embed a process evaluation within the impact evaluation to seek to understand intervention implementation, and document any contextual factors determining the success or failure of delivery of intervention components.

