## Methods

### Study location and non-randomised site selection

We will conduct this study in two DREAMS+PrEP and four non-DREAMS comparison sites. We selected the two DREAMS+PrEP sites, as these sites will refer the largest proportion of young women to PrEP and supportive interventions. These two sites are cities, among the largest in Zimbabwe, with a combined population of over 500,000. Each site has a static *Sisters* programme clinic that offers walk-in clinical services Monday to Friday each week [9].

We selected comparison sites from the 36 sites where the *Sisters* programme is operational [9]. Of the 36 national *Sisters* sites, six are static sites in larger towns and cities that provide walk-in services on weekdays and 30 are mobile sites in smaller towns where outreach services are delivered weekly. From the *Sisters* sites, we first excluded sites that overlapped with DREAMS, excluded seven sites where an HIV treatment and prevention, including PrEP, intervention trial (SAPPH-Ire trial) had been implemented [17], and a site where another organisation is delivering PrEP. Second, we excluded 15 rural sites. From the remaining eight urban sites, we selected four comparison sites using routine *Sisters* programme data and expert opinion. We selected one site as it is a large town with a static *Sisters* clinic where > 1500 FSW were registered by mid-2016, of whom 25% were aged 18 to 24. Of the remaining seven sites we selected three sites because they each had: 1) > 400 FSW registered with the programme; 2) among whom > 20% were aged 18–24, and 3) each site was a similar distance to Harare as the two DREAMS+PrEP sites.

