### Assessing balance across sites

Using enrolment data, we will describe characteristics of the YWSS recruited into the DREAMS+PrEP and non-DREAMS comparison cohorts. To assess whether there is any imbalance across the two cohorts in risk factors for HIV, we will conduct a comparative analysis of the socio-demographic characteristics, sexual behaviours of the YWSS recruited to the impact evaluation, and prevalent and recent infection. Where there is evidence of imbalance in factors likely to influence HIV risk, we will adjust for these individual-level factors in our analysis of the primary outcome as described below.

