### Sample size justification

DREAMS aims to reduce HIV incidence among AGYW by 40%. In the absence of a robust estimate of HIV incidence among the target population, we used data from the *Sisters* programme and the MTN-020 Dapivirine vaginal ring trial to determine the required sample size [9, 30]. A cohort analysis of *Sisters* programmatic data estimated that HIV incidence was 10.8% (95%CI: 8.1–16.1) among FSW aged 18–25 years [9]. In the ASPIRE trial, HIV incidence among women aged 18 to 45 was 4.5 per 100 person-years in the placebo arm, 6.2 per 100 person years in the placebo arms in South Africa, 2.6 in Malawi, Uganda and Zimbabwe [30]. Relative to the target population in our study, women in the ASPIRE trial might have been at lower risk of HIV, with only 7% reporting transactional sex in the previous year. Based on these estimates and assuming individual-level analysis, we assume that incidence among YWSS in the absence of DREAMS+PrEP is between 5.0 and 8.0 new infections per 100 person-years. We also anticipate that, at the point of enrolment, 20% of YWSS will test HIV positive and that 30% of YWSS will be LTFU over the 24-month period. Based on these estimates, we will recruit 1200 YWSS in the DREAMS+PrEP sites and 1200 in non-DREAMS sites to have sufficient person-years of follow-up to have 80% power to detect a reduction of 40% or more in incidence after 24-months at the *p* = 0.05 level (Table 1).

**Table 1 Tab1:** Study power to detect a 30–50% reduction in HIV incidence in DREAMS+PrEP cohort compared to incidence in a comparison cohort with at least 690 YWSS followed up over 24 months (1500–1380 person-years follow-up/cohort)

HIV incidence in comparison cohort	Reduction in HIV incidence in DREAMS+PrEP cohort					
	50%	40%	30%	50%	40%	30%
	1500pyrs follow-up per cohort			1380pyrs follow-up per cohort		
5.0	94	77	49	92	75	46
6.0	96	85	59	96	82	55
7.0	98	90	66	98	87	62
8.0	99	93	72	99	91	67

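### Exposure is set by site (two versus four), but the Poisson rate-ratio interval and the power calculation name no allowance for between-site variation in HIV incidence

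*Protocol article*

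**What the plan says.** The design section states: "We will conduct this study in two DREAMS+PrEP and four non-DREAMS comparison sites". Exposure was not allocated at random; under the key design considerations, "it was not possible to randomise study sites to receive the DREAMS intervention".

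The stages of the primary outcome analysis fix the level of analysis: "In phase one, we will take an individual-level cohort analysis approach". The comparison is then given as "Using Poisson regression, we will compare the incidence rates at 24-months across the two groups expressed as an unadjusted rate ratio with associated 95%CI". The one design adjustment named is for recruitment: "To account for the RDS design, we will weight the data by 1/self-reported degree of social network". Sites enter descriptively: "We will also describe site-specific estimates of incidence". Phase two gives an adjusted rate ratio, and the section on balance says that, where risk factors are imbalanced, "we will adjust for these individual-level factors in our analysis of the primary outcome".

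The sample size section sets the assumed comparison incidence after the words "Based on these estimates and assuming individual-level analysis". It claims 80% power at p = 0.05 for a 40% reduction with 1200 women per group. Table 1 gives the power by incidence, reduction and person-years.

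The analysis section mentions the small number of sites, but only as a reason for confounding.

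**The concern.** Every woman in a site shares that site's exposure status, so the group contrast is a contrast of two towns with four. If underlying incidence differs between towns for reasons unrelated to DREAMS+PrEP, that variation enters the rate ratio. An individual-level Poisson interval does not include it. More women per site reduce the sampling error but not this component.

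Two things are at stake. An ordinary difference between places could exclude a rate ratio of 1 more often than the nominal 5%, and this interval is the first step in the argument for a plausible impact. The published power would also hold only if all six sites shared one underlying rate apart from the intervention effect, which the article does not state as an assumption.

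**Working it through.** **Inputs from the protocol article.** Two exposed and four comparison sites; comparison incidence 6.0 per 100 person-years (within the assumed 5.0 to 8.0); 1380 person-years per cohort (Table 1); rate ratio 0.60 for a 40% reduction; alpha 0.05, taken as two-sided because that reproduces Table 1.

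**Inputs assumed.** Between-site coefficient of variation k of true incidence = 0.10, 0.15 or 0.25; equal site sizes within each group. Neither is in the documents.

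**Step 1: reproduce Table 1.** With independent Poisson events and no site term, power = Φ(|ln RR| / √(1/E0 + 1/E1) − 1.96), where E is rate × person-years.

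- E0 = 0.06 × 1380 = 82.8; E1 = 0.60 × 82.8 = 49.7.
- Variance = 1/82.8 + 1/49.7 = 0.0322; SE = 0.1795.
- |ln 0.60| = 0.511; 0.511/0.1795 = 2.85; power = Φ(0.89) = 81%. Table 1 gives 82%.

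All 24 cells of the table come out within 2 points (largest gap 1.9). The published power therefore contains no allowance for site.

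**Step 2: add between-site variance.** With two and four equal-sized sites:

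Var(ln RR) = 1/E0 + 1/E1 + k²(1/2 + 1/4)

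The added term is 0.0075, 0.0169 or 0.0469 for k = 0.10, 0.15 or 0.25.

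**Step 3: type I error of the nominal 5% test.** Under the null both groups have 82.8 expected events, so the sampling variance is 2/82.8 = 0.0242.

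| k | Total variance | True SE / Poisson SE | 1.96 ÷ ratio | Type I error |
|---|---|---|---|---|
| 0 | 0.0242 | 1.00 | 1.96 | 5% |
| 0.10 | 0.0317 | 1.14 | 1.71 | 9% |
| 0.15 | 0.0410 | 1.30 | 1.50 | 13% |
| 0.25 | 0.0710 | 1.71 | 1.14 | 25% |

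**Step 4: power for a 40% reduction once site variance is in the interval.** The t reference has 6 − 2 = 4 degrees of freedom (critical value 2.776), and power is taken from the noncentral t.

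| k | Total variance | 0.511 / SE | Power, normal reference | Power, t on 4 df |
|---|---|---|---|---|
| 0 | 0.0322 | 2.85 | 81% | 58% |
| 0.10 | 0.0397 | 2.56 | 73% | 50% |
| 0.15 | 0.0491 | 2.31 | 64% | 42% |
| 0.25 | 0.0791 | 1.82 | 44% | 29% |

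The k = 0 row separates two costs. At k = 0.10, the fall from 81% to 50% is 31 points: 23 (81 to 58) come from the t reference and 8 (58 to 50) from site variation.

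**Step 5: effect on an interval.** At an observed rate ratio of 0.60, the Poisson-only 95% interval is 0.42 to 0.85. At k = 0.20 it becomes 0.37 to 0.98 with a normal reference and 0.30 to 1.20 with t on 4 df.

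**The case against.** **The variance estimator is not stated.** The article names Poisson regression, degree weights and a 95% interval, and promises a later SAP. A reader might infer that the interval is certain to contain Poisson error alone. The text does not go that far: an individual-level model can carry a site random effect or a clustered variance, and a weighted model would ordinarily use a robust variance. This stands as a limit on the wording. However, the level of analysis is stated, the only design feature addressed is recruitment, and a robust variance that treats women as independent would still omit site variation. An SAP could add a site-level interval, but would not change the published power.

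**The power assumption is disclosed.** The article does say that it assumes individual-level analysis. It does not say that this means one common rate across sites, or show what follows if that is untrue.

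**Inference is by plausibility, without a significance rule.** This softens the type I error figures, which describe a reject-or-not use of the interval. Site-specific rates, the exposure analysis and the process evaluation also help interpretation. None of them widens the interval, and the sample size is still justified at p = 0.05.

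**Residual k may be small.** Comparison sites were limited to urban ones, three were chosen partly for similar distance to Harare, and phase two adjusts for individual risk factors. This may reduce k, but it does not put the remaining site variance into the interval.

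**Six sites estimate site variance poorly.** True, and it explains why the t-based interval is wide. That is a limit of the design which the reader should see.

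**A permutation floor.** A reader might argue that two exposed sites of six give C(6,2) = 15 allocations, so that no p-value can fall below 1/15. That does not bear on this plan: sites were not randomised and no permutation test is proposed.

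**Conclusion.** The concern holds in a limited form. Exposure is set at site level, the primary comparison is specified at individual level with no named allowance for between-site variation, and the power includes none. The direction is the same for any k above 0: the interval as described is too narrow and the power overstated.

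The size depends on k, which the documents do not supply. For k from 0.10 to 0.25, at 6.0 per 100 person-years, 1380 person-years per cohort and equal site sizes within group, the nominal 5% error is about 9% to 25%, and the 81% power is 73% to 44% with a normal reference. It would be wrong to attribute the whole drop to 50%, 42% or 29% under the t reference to site variation, because that reference alone gives 58% at k = 0.

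This is a should-fix: the point estimate stands, and the correction concerns the interval beside it and the statement of power.

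**What to change.** - Keep the individual-level rate ratio as the point estimate in phases one and two.
- Beside it, in both phases, report an interval that includes between-site variation: either from the six site log-rates (covariate-adjusted in phase two) with t on 4 degrees of freedom, or from a site random effect with small-sample degrees of freedom.
- Label the plain Poisson interval as conditional on these six sites and excluding between-site variation.
- Restate the power claim and Table 1 as assuming no between-site variation. Add sensitivity rows for k = 0.10, 0.15 and 0.25, and show the t-based power at k = 0 so that the two costs can be told apart.

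This needs wording in the analysis plan and one added analysis, with no new data. The price is a wider, less favourable interval and a lower stated power.

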### Measurements and sample collection

Young women recruited to the impact evaluation study will be asked to provide written consent to complete a questionnaire, provide a dried blood spot (DBS) and have a rapid HIV test. Women will be followed-up at 12 and 24 months, and asked to complete an interviewer-administered questionnaire and offered HIV testing services using a rapid HIV test-kit. The questionnaire will cover socio-demographic factors, a range of behavioural characteristics, access to health and/or social-support services, and HIV-related questions. We will use the DBS collected at enrolment to test for HIV, and, for those who test HIV-positive, to determine prevalence of recent infection using Recent Infection Testing Algorithm (RITA), which includes use of the LAG avidity assay coupled with viral load testing.

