### Primary outcome measurement

The primary outcome is HIV incidence over the 24 months following enrolment into the study, the numerator will be the number of new infections among young women testing HIV-negative at enrolment, the denominator the person-years of follow-up. Person-years of follow-up for each YWSS will be calculated as: 1) time between the first HIV negative test at enrolment and an HIV negative test at 12 months and 24 months; or 2) the mid-point between an HIV negative test and an HIV positive test. If a participant is lost to follow-up (LTFU), the participant will be censored at last HIV-negative test.

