We recognise that retention of the YWSS recruited into the cohorts may prove challenging, as such our sample size calculations assume a 30% LTFU over the 24-month study. Furthermore, individuals LTFU may differ in the two groups, leading to bias estimates of HIV incidence. We opted for a cohort design rather than repeat cross-sectional surveys as we are interested in the impact of DREAMS+PrEP among YWSS referred to and offered DREAMS+PrEP services. We recognise that both design options have limitations. Repeat cross-sectional surveys, however, would suffer from issues of temporality, we would not be able to explore individual-level changes over time, and women recruited at successive surveys may have had no exposure to DREAMS+PrEP. Through our cohort study design, YWSS will be referred to and offered DREAMS+PrEP services dependent on need. Our study will therefore allow us to understand women’s level of engagement and reasons for non-engagement with DREAMS.

The DREAMS package of interventions aims to reduce HIV incidence by 40% among AGYW. As such, our study is powered to detect a 40% difference in HIV between the DREAMS+PrEP and non-DREAMS comparison cohorts. This is a large reduction in incidence. If DREAMS+PrEP reduces incidence by 40% we may be able to detect this difference, if levels of LTFU and HIV prevalence at enrolment are as hypothesised, but reductions lower than 40% may not be detected with the proposed sample size. PrEP efficacy studies have shown up to 67% reduction in HIV among sero-discordant couples and young men and women in sub-Saharan Africa [1, 37, 38]. Sub-group analyses suggest efficacy is higher with increased levels of adherence [1, 37]. An offer of PrEP alongside interventions to support retention in or return to school, and improve access to HIV testing, STI screening and treatment among other services are likely to have a large impact on these women’s lives, their access to services and their risk of HIV infection. Should this study be underpowered, it can still provide evidence critical to understanding whether and how DREAMS+PrEP changed young women’s lives and to informing how to provide this underserved and vulnerable population with access to HIV prevention and care services within a broader social support package.

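### The primary Poisson comparison pools 24 months into one rate per group; a follow-up-interval term would be a cheap safeguard against a small shift if incidence changes over time and year-two retention differs

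*Protocol article*

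**What the plan says.** The Protocol article, under Primary outcome measurement, defines the outcome over the whole period: "The primary outcome is HIV incidence over the 24 months following enrolment into the study". New infections are divided by person-years. An infection is dated at "the mid-point between an HIV negative test and an HIV positive test", and for women lost to follow-up "the participant will be censored at last HIV-negative test". Under Measurements and sample collection, testing after enrolment happens twice: "Women will be followed-up at 12 and 24 months".

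Under Stages of primary outcome analysis, phase one is fixed as: "Using Poisson regression, we will compare the incidence rates at 24-months across the two groups expressed as an unadjusted rate ratio". The only modification named there is weighting by the inverse of reported network size. Phase two adjusts for potential confounders. The section Assessing balance across sites describes these as individual-level HIV risk factors found to be imbalanced at enrolment. Time since enrolment is not such a factor, so phase two as described does not bring it in.

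On retention, Sample size justification assumes that "30% of YWSS will be LTFU over the 24-month period", with no split by group or year. The Discussion warns that "individuals LTFU may differ in the two groups, leading to bias estimates of HIV incidence". A separate statistical analysis plan is announced but not shown.

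**The concern.** A pooled rate is a person-time-weighted average of the year-one and year-two rates. If one group keeps more women to 24 months, its average leans more on year two. When the rate differs between years, the ratio of the two averages then differs from the ratio within either year, although nothing about the intervention or about who is lost has changed.

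Incidence could plausibly fall over follow-up: women at highest risk may be infected first, some may stop selling sex, and both groups are referred to services. In that case better retention in the DREAMS+PrEP sites would pull the ratio towards apparent benefit, and worse retention would dilute a real effect. If incidence rises, the directions reverse. A larger sample does not shrink such a shift. A single pooled figure also hides whether an effect emerges only after services have been taken up, which the article's plausibility-based inference could use.

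**Working it through.** **Inputs from the article.** 1200 women per group, 20% HIV-positive at enrolment, so 1200 × 0.8 = 960 at risk; comparison incidence 5.0 to 8.0 per 100 person-years; target rate ratio 0.60; tests at 12 and 24 months; mid-point dating; censoring at the last negative test.

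**Inputs assumed, because the article does not give them.** Incidence by year of follow-up, and retention by group and year.

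**Scale of random error.** A Wald calculation on the log rate ratio reproduces every cell of the article's Table 1 to within 2 points. At 5.0 per 100 person-years, 1500 person-years and a 40% reduction, expected infections are 75 and 45. The standard error is √(1/75 + 1/45) = 0.189, the 95% CI around 0.60 is about 0.41 to 0.87, and power is 77.3% against 77 in the table.

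**General formula.** Let P1 be the proportion contributing year one (equal in both groups), A and B the proportions contributing year two in the DREAMS+PrEP and comparison groups, and c the year-two rate divided by the year-one rate. If the true rate ratio is the same in both years, then approximately

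pooled RR / true RR = [(P1 + cA)/(P1 + A)] ÷ [(P1 + cB)/(P1 + B)].

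This equals 1 if c = 1 or A = B. With P1 = 0.85:

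| A v B | c | Factor | True 0.60 reads as |
|---|---|---|---|
| 0.75 v 0.65 | 0.5 | 0.7656/0.7833 = 0.977 | 0.586 |
| 0.75 v 0.65 | 0.8 | 0.9063/0.9133 = 0.992 | 0.595 |
| 0.80 v 0.60 | 0.5 | 0.7576/0.7931 = 0.955 | 0.573 |
| 0.60 v 0.80 | 0.5 | 0.7931/0.7576 = 1.047 | 0.628 |
| 0.80 v 0.60 | 1.5 | 1.2424/1.2069 = 1.029 | 0.618 |

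**Expected counts under the article's dating and censoring rules.** Take 960 women per group, no effect, and incidence of 8 then 4 per 100 person-years. In each group 85% are tested at 12 months; of those still negative, 95% (DREAMS+PrEP) v 65% (comparison) are tested at 24 months.

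- Year one, each group: 62.74 infections in 784.63 person-years.
- Year two: 28.06 in 701.57 (DREAMS+PrEP) and 19.20 in 480.02 (comparison).
- Pooled: (90.80/1486.20) ÷ (81.94/1264.65) = 0.0611/0.0648 = 0.943.
- Stratified by year (Mantel-Haenszel): 1.000.

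Other cases with no true effect:

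| Incidence, year 1 to year 2 | Retention 95% v 65% | Reversed |
|---|---|---|
| 8 to 4 | 0.943 | 1.060 |
| 8 to 5 | 0.960 | 1.042 |
| 7 to 5 | 0.970 | 1.031 |
| constant 6 | 1.000 | 1.000 |

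With 88% v 76% the 8-to-4 result is 0.977. A true 0.60 in the 8-to-4 case with 95% v 65% reads as 0.564 (0.634 reversed); stratified it is 0.600.

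**Precision.** In a simulation with 960 per group, a true ratio of 0.60, incidence of 6 then 3, and 80% v 60% retained in year two, the standard error of the log rate ratio was 0.1985 without the interval term and 0.1990 with it.

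**Women who miss month 12 but return at month 24.** If such a woman tests positive, the mid-point rule dates her infection at exactly 12 months, the boundary between intervals. Assume a true ratio of 0.60, incidence 6 then 3, 75% seen at 12 months, 85% v 65% of those still negative seen at 24 months, and 60% v 40% of the women who missed month 12 returning. About 15% of infections are then ambiguous. The pooled ratio is 0.577. With the interval term it is 0.608 if these infections go to year one, 0.585 if they go to year two, and 0.596 if half go to each.

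**Effect that differs by year.** With true ratios of 0.8 then 0.4 and comparison incidence of 8 then 5, the pooled ratio moves from 0.627 to 0.715 when the 95/65 split is reversed. The stratified ratio stays at 0.674 to 0.675, a weighted average that equals neither year's ratio.

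**The case against.** The strongest reply is that this is a condensed article with an analysis plan to follow, and that time terms usually belong in that plan. Phase one is deliberately simple and labelled unadjusted, and the article promises to report retention and follow-up time by group, so unequal follow-up would be visible. Much of this stands. The absence of an interval term is not an omission to hold against the article. What remains is that the article does state a model (one pooled rate per group) and describes an adjustment set that does not reach follow-up time, so a better version of the stated model can be offered.

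A second objection, that the shift is negligible beside the confidence interval, is fair as to size. The shift is systematic, however, and removing it costs little.

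A reader might infer more than the documents support:

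- That the primary ratio is biased. No figure in the article shows that incidence changes over follow-up or that retention differs by group. The Discussion's warning, "individuals LTFU may differ in the two groups, leading to bias estimates of HIV incidence", mainly concerns who is lost, which is a different problem.
- That a year term removes the shift at no cost. Exact removal needs the same rate ratio in both years and loss unrelated to risk within each year. Infections dated at month 12 also need an allocation rule, and that choice alone moved the estimate between 0.585 and 0.608 for a true 0.60.
- That the term deals with informative loss. It does not.

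**Conclusion.** The point holds as a modest improvement. The pooled Poisson ratio is shifted by about 1 to 6% in the assumed scenarios, in either direction, and not at all if incidence is constant or the groups divide their person-time between years in the same way. The upper end needs both a halving of incidence and a wide gap in retention: 0.85 × 0.95 = 81% v 0.85 × 0.65 = 55% tested at both visits. Every shift shown lies well inside the 0.41 to 0.87 interval that random error alone gives around 0.60.

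An interval term largely removes the shift when the rate ratio is similar in the two years. Otherwise it gives a weighted average that depends far less on retention than the pooled ratio does in the example shown. The low priority reflects the small size and the reliance on rates and retentions that the documents do not supply.

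**What to change.** In Stages of primary outcome analysis, or in the analysis plan before the 24-month data are complete:

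1. Keep the pooled unadjusted ratio as the phase-one description.
2. Split each woman's person-time at 12 months and include follow-up interval (0–12, 12–24 months) as a term in the Poisson model, at least in phase two.
3. Report rates and rate ratios for each interval beside the pooled ones.
4. State how infections are allocated for women who missed the 12-month test and were positive at 24 months, for example half to each interval.
5. Say that the combined ratio is a weighted average if the effect differs by interval, and that loss related to HIV risk needs separate handling.

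The cost is one model term, one allocation rule and a few lines of text, with no new data and a negligible loss of precision (standard error 0.1985 to 0.1990 in the case simulated).
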